#### 6.4.2. Laboratory Examination

Lab examination includes blood hematology, blood biochemistry, urine analysis during the screening visit. Descriptive analysis will be performed to summarize the results and clinical significance judgment of lab examination. For blood hematology, blood biochemistry, urine analysis, listings of patients with clinical significance results will be provided. The listings will be presented according to the subject ID, sex, age, date of test, examination index, examination result and/or clinical evaluation.

All measures will be summarized by use of standard measures of central tendency and dispersion using mean and standard deviation as well as quartile points at 0.25, 0.5 and 0.75 where appropriate stratified by measurement time points and by treatment group. Longitudinal mean plots will be used to display means and 95% confidence bands over time by randomized group. To assess the treatment effect on laboratory variables, a linear mixed effects model with a random intercept by subject and with treatment, time (categorical) and a treatment by time interaction as fixed effects will be used. The effect of the treatment will be assessed as the adjusted mean difference and its 95% confidence interval.

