#### 7.4 Sample size

The sample size is estimated before the study with the use of nQuery Advisor software. Our preliminary study of IgA nephropathy showed that the three-year rate of the primary endpoint (doubling of serum creatinine, end-stage renal disease, and death) among patients with IgA nephropathy taking RAS inhibitors was 36%. It is estimated that MMF treatment will reduce this rate to 16%. Thus, the enrollment of 76 per group will provide the study with a statistical power of 80% at a two-sided significance level of 0.05. Considering 10% of participants lost to follow-up over 3 years, the final sample size was 84 per group.

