## 3. Study Design

This study is a prospective, open-label, randomized controlled, blinded endpoint (PROBE) trial. This trial will include participants with IgA nephropathy who are at a high risk of disease progression.

Patients with IgA nephropathy were recruited at the renal division of Nanfang Hospital, Southern Medical University. After recruitment, the patients first entered into a 12-week run-in period, during which the patients were treated with comprehensive supportive care, including blockade of RAS using maximum tolerable daily dose of losartan to reduce blood pressure to a target below 130/80 mmHg and a urine protein excretion (UPE) below 0.75g per day. The participants were also advised for lifestyle modification, including quitting smoking, restricting high-salt intake, and avoiding nephrotoxic drugs. Anemic patients with a hemoglobin level lower than 110g/L were treated with erythropoietin. Statin was used when necessary. Dietary sodium intake were monitored by urinary sodium excretion rate (or chloride excretion rate in patients treated with sodium bicarbonate) measured by 24-hour urine sample.

The patients who were tolerable to losartan (<30% eGFR decline and without hyperkalemia) and proteinuria (0.75-3.5 g/day) at the end of run-in period were randomized to receive MMF plus supportive care or supportive care alone. The MMF plus supportive care group received a daily oral dose of 1.5g MMF for the first 12 months, followed by a maintenance daily dose of 0.75g to 1.0g for at least 6 months. Both MMF plus supportive care and supportive care alone group stayed on supportive care as in the run-in period. All participants were followed up at regular intervals for 3 years.

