### 3.7.2. Laboratory Examination

Lab Examination during the screening visit are as following.

- Blood hematology: counts of red blood cells, white blood cells, neutrophil count, lymphocyte count, platelets, hemoglobin
- Blood biochemistry: serum creatinine, urea nitrogen, uric acid, total carbon dioxide, potassium, sodium and chlorine, alanine aminotransferase, aspartate aminotransferase, albumin, total bilirubin, triglyceride, cholesterol, very low density lipoprotein, high density lipoprotein, low density lipoprotein, calcium, phosphorus, fasting glucose
- Routine urinal assays: urine protein, white blood cells per high power field (WBCs/HPF) and red blood cells per high power field (RBCs/HPF)
- 24-hour UPE rate
- Scoring of histological lesions

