### **4.3. Handling of Missing Data**

For primary and secondary endpoints, missing data will be treated as missing, and no imputations will be performed.

Counts of missingness will be reported in descriptive analysis of categorical variables, and percentages of the non-missing categories will be based on all values. For continuous variables, the number of non-missing values as well as missing values will be reported, but descriptive summaries will be based on the number of non-missing values.

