#### **6.3.3.2. Annual Absolute Change in eGFR (eGFR Slope)**

The eGFR slope of each participant in ITT during the trial period will be estimated using a linear mixed effect model with random intercept and random slope. The difference in the eGFR slope between the two treatment groups will be estimated and tested using a linear mixed effect model with an interaction term between treatment group and time.

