### **6.4. Safety Analysis**

The analysis of safety endpoints will be performed on the SS. For safety analysis, no formal hypothesis testing will be performed. Descriptive analysis will be performed to summarize safety events. Serious adverse events and adverse events will be summarized as the number of events and the number (%) of patients experiencing at least one event. Differences in the proportions of patients experiencing at least one event will be tested using Fisher's exact test.

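### The random-intercept laboratory model gives 95% intervals that are too narrow late and too wide early for variables whose patients diverge, most plainly serum creatinine

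*Combined protocol and SAP*

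**What the plan says.** SAP 6.4.2 models laboratory variables with "a linear mixed effects model with a random intercept by subject and with treatment, time (categorical) and a treatment by time interaction" as fixed effects, and adds: "The effect of the treatment will be assessed as the adjusted mean difference and its 95% confidence interval". It does not say whether that difference is taken visit by visit, as a change from baseline, or averaged over visits. It specifies no covariance beyond the random intercept.

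The variables are listed in SAP 3.7.2 and begin: "Blood biochemistry: serum creatinine, urea nitrogen, uric acid, total carbon dioxide, potassium". That list is headed as screening tests, but 6.4.2 summarises by measurement time point, and Table 1 has blood chemistry at all 24 visits from week 0 to week 156.

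For eGFR, by contrast, SAP 6.3.3.2 uses a "linear mixed effect model with random intercept and random slope", and 6.3.3.3 counts patients by their individual slopes. On the status of the safety analyses, SAP 6.4 states: "For safety analysis, no formal hypothesis testing will be performed".

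**The concern.** With only a random intercept and independent residuals, the model assumes that patients are equally spread at every visit and that any two visits are equally correlated, whether 4 weeks or 3 years apart. If patients follow different trajectories, the true spread of values and of changes grows with time. The fitted model then applies one averaged variance everywhere, which is too small late and too large early.

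The documents themselves point to divergence in kidney function. SAP 6.1 derives baseline eGFR from serum creatinine, and 6.3.3.2 lets eGFR slopes differ between patients. Protocol 7.4 assumes that 36% of controls reach an endpoint including doubling of creatinine or ESRD within three years, so 64% do not. Yet creatinine as a laboratory variable goes into the random-intercept model.

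Two errors are at stake. Late differences would look more certain than they are. Early ones would look less certain, and Table 1 dispenses study drug only up to week 78, so much of the exposure period falls where intervals are too wide.

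**Working it through.** The plan gives no SD, standard error or coverage for this model, so there is no stated figure to reproduce. The SDs below are assumptions, and only their ratios matter. The group size of 84 (protocol 7.4) cancels out of coverage.

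**Visit times (SAP Table 1).** Weeks 0, 4, 8, 12, 16, 20, 28, 36, 44, 52, 60, 68, 76, 78, 86, 94, 102, 110, 118, 126, 134, 142, 150 and 156. With t in years, mean(t) = 1.378, mean(t²) = 2.792 and sample variance V = 0.931.

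**Truth.** Intercept SD σ0, slope SD σ1 per year, residual SD σe, independent residuals, zero intercept-slope correlation:
- variance at a visit: σ0² + σ1²t² + σe²
- variance of change from baseline: 2σe² + σ1²t²

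**What the random-intercept model estimates from complete data.**
- residual variance: σe² + σ1²V
- variance at any visit: σ0² + σ1²·mean(t²) + σe²
- variance of any change: 2(σe² + σ1²V)

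Coverage = 2Φ(1.96 × SE_model / SE_true) − 1.

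**Where the error changes sign.** Change intervals are too narrow when t² > 2V, that is after week 52 × √(2 × 0.931) = 71. The first such visit is week 76, so 12 of 23 post-baseline visits are affected. Visit differences are too narrow when t² > mean(t²), that is after week 52 × √2.792 = 87. The first such visit is week 94, so 9 of 24 are affected. If week 0 is left out of the outcome, that threshold moves only to week 89.

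**Worked example: σ0 = 14, σ1 = 4, σe = 4, 84 per arm.**
- Visit difference, week 156. Model variance 196 + 16 × 2.792 + 16 = 256.7, SE √(2 × 256.7/84) = 2.47. True variance 196 + 16 × 9 + 16 = 356, SE 2.91. Ratio 0.849, coverage 90.4%.
- Change, week 156. Model variance 2(16 + 16 × 0.931) = 61.8, SE 1.21. True variance 32 + 144 = 176, SE 2.05. Ratio 0.593, coverage 75.5%.
- Change, week 4: coverage 99.3%. Change, week 52: true variance 32 + 16 = 48, SE 1.07, coverage 97.4%. Both intervals are too wide.
- Average over visits. True variance 196 + 16 × 1.378² + 16/24 = 227.1, and the model gives the same, so both SEs are √(2 × 227.1/84) = 2.33.

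**Week-156 coverage by slope SD (σ0 = 14, σe = 4).**

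| Slope SD per year | Visit difference | Change from baseline |
|---|---|---|
| 0 | 95.0% | 95.0% |
| 1 | 94.7% | 92.5% |
| 2 | 93.7% | 86.5% |
| 3 | 92.2% | 80.2% |
| 4 | 90.4% | 75.5% |

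With σ0 = 14, slope SD 3 to 6 and residual SD 3 to 5, coverage is 86–92% for the visit difference and 67–84% for change. The standard errors are 10–24% and 29–50% too small.

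**Sensitivity.** The change result does not depend on the intercept SD or the intercept-slope correlation. The visit result does: with 15/4/5 (intercept, slope, residual SD), week-156 coverage is 89.5% at correlation 0.3, 93.0% at −0.3 and 96.0% at −0.6. A smaller intercept SD makes it worse: 80.4% with 5/5/5.

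**Simulation check.** For 15/3/5, the closed form gives 92.6% (week 156), 83.8% (change at week 156) and 97.6% (change at week 4). Simulating 1,500 trials with 10% dropout gives 92.6%, 82.1% and 97.5%, and 95.3% for the average over visits.

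**The case against.** The strongest defence is that the SAP never names a week-156 or change-from-baseline contrast. If the adjusted mean difference is the average over visits, its interval is about right. That stands. However, a model with categorical time and a treatment-by-time interaction naturally yields a difference at each visit, and the SAP's silence leaves the choice open.

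Second, these are descriptive safety analyses, so a reader who calls these intervals the formal test of laboratory effects goes beyond SAP 6.4. This stands and limits the impact. It is not a full answer: SAP 4.4 sets a p < 0.05 threshold for safety analyses, 6.4 plans Fisher's exact tests, and an interval labelled 95% should cover about 95%.

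Third, divergence is supported only for kidney function. Nothing in the documents shows it for potassium, sodium, ALT, white cells or platelets. Without divergence the planned model is correctly calibrated. This also stands.

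A reader might infer that all change-from-baseline intervals are too narrow, or that laboratory differences would be declared too often in general. The visit schedule does not support that. Before about week 71 the change intervals err in the cautious direction, and in the worked example mean coverage of the visit differences over all 24 visits is 94.9%. A reader might also extend the point to the confidence bands on the mean plots, but 6.4.2 introduces those before the model and does not say they come from it.

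**Conclusion.** The point holds in limited form. For laboratory variables whose patients diverge, the model in SAP 6.4.2 gives miscalibrated intervals. Late change from baseline is the serious case, and the late visit difference loses only modestly unless slope spread is large relative to the other SDs. Early intervals are too wide.

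The direction and timing for change follow from the Table 1 schedule. The timing for visit differences also needs an intercept-slope correlation near zero, and a strongly negative one can reverse it. All coverage figures rest on assumed SDs, linear divergence, independent residuals and model-based standard errors; the last two are the plain reading of 6.4.2 but are not stated there. Creatinine is the only variable for which the documents give a clear reason to expect divergence, together with urea nitrogen to the extent that it tracks kidney function. Primary and secondary efficacy analyses are unaffected, and kidney function is already assessed there by the random-slope eGFR model and the time-to-event endpoints. Impact is low to moderate.

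**What to change.** Amend SAP 6.4.2 in two respects.

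- State which contrast is the reported laboratory effect: the difference at each visit, the difference in change from baseline, or the difference averaged over visits.
- For the model-based contrasts, replace the random-intercept-only covariance with an unstructured covariance or with a random intercept and slope, or keep the mean model and use cluster-robust standard errors. Any one of these addresses the problem. A random slope matches the SAP's own eGFR model but assumes linear divergence. An unstructured covariance avoids that assumption, but with 24 visits it has 24 × 25/2 = 300 parameters, so a fallback should be named in case it does not converge. Robust standard errors are the simplest change.

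If the mean-plot bands are meant to come from this model, say so and treat them the same way. The cost is a line or two of SAP text and model code, with somewhat wider late intervals for variables that diverge. No data collection or sample size changes.

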### **5.2. Safety Set (SS)**

SS is a subset of ITT. It consists of ITT participants excluding the ones without taking any study medication or having no record of follow up after randomization. SS will be used for the safety analysis.

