## **6. Statistical Analyses**

### **6.1. Population Characteristics at Randomization**

The demographic and clinical characteristics of the ITT set at randomization stratified by the treatment group will be summarized. Summary statistics for quantitative variables will include N, mean, SD, or median, Q1, Q3. Summary statistics for qualitative variables will be N (%) for each level. Unless otherwise specified, the calculation of proportions will be based on the non-missing data. Difference in the variable distribution between the two treatment groups will be tested using the unpaired two-sample t-test (quantitative variables) and the chi-square test (qualitative variables). The following variables will be analyzed:

- Demography: age, sex, BMI.
- Comorbidity: smoking status, macrohematuria, history of hypertension, other reported medical history and co-morbidities.
- Vital Signs: body temperature (°C), pulse (beats/min), blood pressure (mmHg), respiratory rate.
- Use of Medications: anti-hypertensive drugs and types; statin.
- Baseline serum creatinine and eGFR. The baseline creatinine is calculated as the mean of the two creatinine values from Visit 4 (pre-randomization visit) and Visit 5 (randomization visit). Baseline eGFR is calculated from baseline serum creatinine using the CKD-EPI equation
- Other laboratory results:
  - Hematology: hemoglobin, white blood cell count, lymphocyte and platelet count
  - Blood chemistry: urea nitrogen, uric acid, total carbon dioxide, potassium, sodium and chlorine, alanine aminotransferase, aspartate aminotransferase, albumin, total bilirubin, triglyceride, cholesterol, very low density lipoprotein, high density lipoprotein, low density lipoprotein, calcium, phosphorus, glucose
  - Urinary analysis: white blood cells per high power field (WBCs/HPF) and red blood cells per high power field (RBCs/HPF)
  - 24-hour UPE

- Pathological features: percentage of glomeruli with global glomerulosclerosis, percentage of glomeruli with segmental glomerulosclerosis, mesangial hypercellularity, endocapillary hypercellularity, tubular atrophy/interstitial fibrosis, percentage of glomeruli with crescents; MEST-C Oxford Score.

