## **6.3. Efficacy Analyses**

### **6.3.1. Main Analyses of the Primary Outcomes**

- The number of the composite outcome (primary outcome 1) and its components by each treatment group in ITT.
- The number of disease progression (primary outcome 2) by each treatment group in ITT.
- Kaplan-Meier curves of cumulative survival rates of the two primary outcomes by two treatment groups in ITT.
- To perform log-rank tests on the two primary outcomes between the two treatment groups in ITT. A p-value of 0.025 will be regarded as statistically significant.
- Estimate the hazard ratios (and 95% confidence intervals) of the treatment for the two primary outcomes, respectively, using the Cox proportional hazard models, with and without covariate adjustment. The adjusting covariates include age, sex, BMI, SBP, eGFR, logarithm of UPE rate and individual Oxford MEST-C scores at baseline.

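### The laboratory model in SAP 6.4.2 omits the baseline laboratory value and leaves its treatment contrast undefined, so its estimates are generally less precise than the collected data allow

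*Combined protocol and SAP*

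**What the plan says.** SAP 6.4.2 (Laboratory Examination) specifies "a linear mixed effects model with a random intercept by subject", and states that "treatment, time (categorical) and a treatment by time interaction as fixed effects will be used". It then says: "The effect of the treatment will be assessed as the adjusted mean difference and its 95% confidence interval". No baseline laboratory value or other covariate is listed.

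Three things are left open: whether the randomization visit is a level of time, whether the reported difference is per visit, averaged over visits or a change from baseline, and what baseline means for most laboratory variables. SAP 6.1 defines baseline creatinine (the mean of Visits 4 and 5), and SAP 6.3.3.4 does the same for 24-hour protein excretion. For the rest, SAP 6.1 only names the variables, for example "Hematology: hemoglobin, white blood cell count, lymphocyte and platelet count".

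Table 1, in both the protocol and the SAP, marks hematology and blood chemistry at Visit 5 (week 0) and at each of Visits 6 to 28. The adjusted efficacy models do name their covariates; SAP 6.3.1 states: "The adjusting covariates include age, sex, BMI, SBP, eGFR, logarithm of UPE rate and individual Oxford MEST-C scores at baseline". On the status of the analysis, SAP 6.4 says: "For safety analysis, no formal hypothesis testing will be performed".

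**The concern.** The result is described as adjusted, but the listed terms contain nothing to adjust for beyond treatment, time and their interaction. A random intercept models the correlation among a patient's repeated values; it does not take the place of a baseline covariate.

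This matters because the model is the only planned between-arm comparison of laboratory values that yields an effect estimate. Leukopenia and transaminase elevation are adverse events of special concern in SAP 6.4.1, and the protocol's safety endpoints add anemia. In a descriptive analysis the estimate and its interval are the result. Width that a value already collected could remove is therefore worth removing, and a reader needs to know which difference is being reported.

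**Working it through.** **Inputs.** The model terms come from SAP 6.4.2, the visits from Table 1, and 84 per group from protocol 7.4. The documents give no laboratory standard deviation, within-patient correlation ρ or target interval width. I therefore work in SD units and assume ρ between 0.3 and 0.9, with equal variance at all visits and the equal correlation that a random intercept implies.

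**The plan's own figure.** None exists for the laboratory model. The only design figure is the primary-endpoint sample size. For 36% against 16%, two-sided 0.05 and 80% power, the pooled formula gives 75 per group (stated: 76; power at 76 is 80.9%), and 75/0.9 rounds up to the stated 84. This has no bearing on the present point except to supply n.

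**What the model estimates.** A generalized least squares fit to simulated complete data (84 per arm, ρ = 0.7) gave an arm difference at every visit equal to the raw difference in means, with gaps below 1e-13. The equality has two limits:
- With dropout depending on observed values (12% and 14% of patients in two simulated sets), the model estimate departed from the raw difference by up to 0.06 and 0.12 SD.
- With Visit 5 as a time level, the treatment-by-time contrast equals the difference in change from baseline.

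**Variance of a single-visit difference, n per arm, SD = 1.**
- Raw contrast: 2/n
- Change contrast: (2/n) × 2(1 − ρ)
- Baseline-adjusted: (2/n) × (1 − ρ²)

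Since 1 − (1 − ρ²) = ρ² and 2(1 − ρ) − (1 − ρ²) = (1 − ρ)², the adjusted variance never exceeds either alternative (ignoring the small cost of estimating the slope). With n = 84, the raw 95% half-width is 1.96 × √(2/84) = 0.302 SD.

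| ρ (assumed) | Half-width, raw | Half-width, change | Half-width, adjusted | SE ratio raw/adjusted | SE ratio change/adjusted |
|---|---|---|---|---|---|
| 0.3 | 0.302 | 0.358 | 0.289 | 1.05 | 1.24 |
| 0.5 | 0.302 | 0.302 | 0.262 | 1.15 | 1.15 |
| 0.7 | 0.302 | 0.234 | 0.216 | 1.40 | 1.08 |
| 0.9 | 0.302 | 0.135 | 0.132 | 2.29 | 1.03 |

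The simulated fit at ρ = 0.7 gave a standard error of 0.120 for the change contrast, matching √((2/84) × 0.60), and 0.154 for the raw contrast.

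**Average over the 23 post-randomization visits (6 to 28).** Let M = (1 + 22ρ)/23. In units of 2/n the variances are M (raw), M + 1 − 2ρ (change) and M − ρ² (adjusted). At ρ = 0.7 these are 0.713, 0.313 and 0.223, so the SE ratios are 1.79 and 1.18. From ρ = 0.3 to 0.9 the raw ratio runs from 1.17 to 3.10 and the change ratio from 1.74 to 1.05. These figures rest on one constant correlation over 156 weeks and on an average that the SAP does not name.

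**Time window.** Table 1 marks study drug dispensation at Visits 6 to 18 (weeks 4 to 78). Visits 19 to 28 are 10 of the 23, so an average over all visits would mix the two periods.

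**The case against.** A reader might infer that the reported difference is adjusted for nothing and is simply the raw arm difference. The SAP does not settle that. If week 0 is a time level and the interaction is reported, the estimate already uses baseline through the change. The gain from a covariate is then modest at high correlation: at ρ = 0.7 the interval narrows by about 8% (0.234 to 0.216), against 29% from the raw contrast (0.302 to 0.216). The equality with the raw difference also needs complete data, and protocol 7.4 expects 10% loss to follow-up. This objection stands, and is why the point includes the undefined contrast. It does not remove the point, because the covariate model is at least as precise under either reading.

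A reader might also infer that the estimates are confounded by baseline. They are not: allocation is randomized 1:1, a chance imbalance is not confounding, and the unadjusted interval already allows for it. SAP 6.1 also compares baseline laboratory values between arms, so an imbalance would be visible.

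Finally, a reader might infer that the effects are estimated too imprecisely, or that a harm would be missed. The documents set no precision or power target for laboratory variables and call the safety analysis descriptive, so there is nothing to judge that against. Laboratory harms are also covered elsewhere: by adverse-event proportions compared with Fisher's exact test (SAP 6.4) and by listings of clinically significant results (SAP 6.4.2).

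**Conclusion.** The point holds as a matter of efficiency and specification, not validity. SAP 6.4.2 omits a baseline value that Table 1 already collects and does not define its contrast. Both plausible contrasts are unbiased under randomization. Relative to a baseline-adjusted model, the single-visit standard error is 1.05 to 2.29 times as large for the raw contrast and 1.24 down to 1.03 times for the change contrast, as ρ goes from 0.3 to 0.9.

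These ratios rest on an assumed ρ, equal variances and equal correlation, but not on n. The half-widths do depend on n, and 84 is the planned number randomized rather than the analyzed number. The safety set is smaller by definition: "It consists of ITT participants excluding the ones without taking any study medication or having no record of follow up after randomization". How that wording applies to the supportive-care arm is a separate question. Priority is low: a worthwhile refinement to a descriptive analysis.

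**What to change.** In SAP 6.4.2:

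- Use post-randomization values as the response, and add the baseline value of the same laboratory variable and baseline-by-time as fixed effects. Alternatively, keep baseline as a response with a common mean across arms, which retains patients who lack a baseline value.
- Define baseline as Visit 5. For creatinine, keep the SAP 6.1 definition (mean of Visits 4 and 5) and reconcile it with Table 1, which marks no blood chemistry at Visit 4.
- Name the reported contrast. Report it by visit, or separately for visits up to and after Visit 18, the last dispensing visit in Table 1.
- Do not label the later visits off-drug yet. Protocol 7.1 and 7.9 give the maintenance phase a minimum length and no maximum, while Table 1 stops dispensing at Visit 18. Those passages must be reconciled first.

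The cost is SAP wording and slightly more analysis work. No new data are needed. The covariate version loses patients without a baseline value; the common-mean version does not.
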